
### 2.4 Treatments

#### 2.4.1 Atezolizumab

Patients will receive atezolizumab every 3 weeks, at fixed dose of 1,200 mg in 60-min intravenous (IV) infusion before UCPVax injection, until disease progression or unacceptable toxicity or maximum of 2 years. If atezolizumab is well tolerated at the first cycle, atezolizumab perfusion can be reduced to 30 min in the following cycles. No dose adjustment is required. No premedication treatment is required before infusion of atezolizumab.

#### 2.4.2 UCPVax

UCPVax is a telomerase-derived cancer vaccine developed by our academic research network at Besançon (Pr [name], UMR1098 INSERM/EFS/UFC) and patented (n° EP: 12305319 and n° US: 61/621.075) by a consortium including the Regional University Hospital of Besançon and the University of Bourgogne Franche-Comté.

The Good Manufacturing Practice (GMP) drug substance of UCPVax was produced by PolyPeptide biotech (Strasbourg, France). Clinical grade peptide production and formulation will be performed according to GMP preparation and compliance by the Pharmacy Department of the University Hospital of Besançon like in the previous trial in lung cancer (Clinical Trial NCT02818426).

The two UCPVax peptides, UCP2 and UCP4 at 1 mg/ml (combined with Montanide ISA51 as adjuvant), will be injected subcutaneously in two separate sites (one site per peptide) (**Figure 1**) at days 1, 8, 15, 29, 36, and 43 (priming phase) following by boost vaccinations: every 6 weeks for the two first boosts (W13 and W19) and every 9 weeks afterward (W28, W37, and W46).

**Figure 1 f1:**
[figure not shown]
Injection sites of each peptide. The two UCPVax peptides, UCP2 and UCP4 at 1 mg/ml (combined with Montanide ISA51 as adjuvant), will be injected subcutaneously in two separate sites (one site per peptide) at days 1, 8, 15, 29, 36, and 43 (priming phase) following by boost vaccinations: every 6 weeks for the two first boosts (W13 and W19) and every 9 weeks afterward (W28, W37, and W46).

### 2.5 Study Description

#### 2.5.1 Therapeutic Sequence

Initial assessments will be performed at baseline, within 28 days prior to the first administration of the combination atezolizumab and UCPVax. Treatment will include three phases (**Figure 2**):

**Figure 2 f2:**
[figure not shown]
Therapeutic sequences. **Part 1** Induction phase: Atezolizumab (1,200 mg IV) will be administrated every 3 weeks starting at day 1. UCPVax will be injected subcutaneously at weeks 1, 2, 3, 5, 6, and 7. The two peptides included (UCP2 and UCP4) in UCPVax will be injected subcutaneously in separate sites (one site per peptide) after emulsion in the adjuvant (Montanide ISA-51 VG). **Part 2**: Boost phase of UCPVax+. Atezolizumab: Atezolizumab will be administered at the standard dose of 1,200 mg IV every 3 weeks. UCPVax boosts vaccine will be performed every 6 weeks for the two first boosts (W13 and W19) and then every 9 weeks thereafter (W28, W37, and W46). **Part 3**: Atezolizumab in monotherapy will be administrated every 3 weeks until disease progression or unacceptable toxicities for a maximum of 1 year since the last vaccine.

##### - Part 1: Induction phase of UCPVax + Atezolizumab

Atezolizumab, 1,200 mg IV, will be administrated every 3 weeks starting at day 1. UCPVax will be injected subcutaneously (according to previous phase I/II study) at weeks 1, 2, 3, 5, 6, and 7. The two peptides included (UCP2 and UCP4) in UCPVax will be injected subcutaneously in separate sites (one site per peptide) after emulsion in the adjuvant (Montanide ISA-51 VG). Tumor assessment will be made according to iRECIST criteria every 8 weeks with a total body CT scan (if progressive disease, it could be confirmed by another total body CT scan 4 to 8 weeks after the precedent).

##### - Part 2: Boost phase of UCPVax + Atezolizumab

Only patients with stable, partial, or complete response at disease evaluation visit at 4 months will be included to Part II. Atezolizumab will be administered at the standard dose of 1,200 mg IV every 3 weeks. UCPVax boosts vaccine will be performed every 6 weeks for the two first boosts (W13 and W19) and then every 9 weeks thereafter (W28, W37, and W46).

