#### 2.5.2 Evaluation, Laboratory Tests and Follow-Up

For the primary end-point analysis, a total body CT scan will be performed at baseline, and every 8 weeks until progression. Additional total body CT scan could be performed if clinically indicated.

For immunological safety assessment, three blood samples will be collected:

Sample N°1: At inclusion visit before the first treatmentSample N°2: At week 5 (before vaccination n°4)Sample N°3: At 2 months from inclusion

In case of immune-related adverse event, these analyses will be performed:

- Immunological blood analysis: IgG, IgE, circulating antibodies (ANA and TPO), CRP, and ferritin. Serum (one dry tube, 6 ml) will be frozen for the measure of anti-telomerase peptide (anti-UCP) antibodies.- Cytokines release measurement (one EDTA tube, 6 ml): Plasma will be frozen for analysis of IL-1b, IL-6, IL-8, IL-2, TNFα, IFN-g, IL-17, and sCD25.

For immunomonitoring analysis, four blood samples will be collected at the following:

Sample N°1: at baselineSample N°2: at 2 months from inclusionSample N°3: at 4 months from inclusionSample N°4: at the end of vaccine visit

Biomonitoring Blood Samples: Six 6-ml EDTA tubes for PBMC collection, one 6-ml EDTA tubes for plasma collection, and one 6-ml EDTA tube for ctDNA collection will be collected for analysis.

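### Entry to the boost phase depends on the 4-month evaluation, but the first boost is due at week 13, which precedes that evaluation in all but a limit case

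*Protocol article*

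**What the plan says.** Section 2.5.1 divides treatment into three parts. Part 1 (induction) gives the vaccine over the first seven weeks: "UCPVax will be injected subcutaneously (according to previous phase I/II study) at weeks 1, 2, 3, 5, 6, and 7". It also sets the imaging interval: "Tumor assessment will be made according to iRECIST criteria every 8 weeks with a total body CT scan". Section 2.5.2 gives the same interval for the primary endpoint: "a total body CT scan will be performed at baseline, and every 8 weeks until progression".

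Part 2 (boost) opens with a condition: "Only patients with stable, partial, or complete response at disease evaluation visit at 4 months will be included to Part II". Two sentences later it gives the calendar of the boosts that make up this part: "UCPVax boosts vaccine will be performed every 6 weeks for the two first boosts (W13 and W19"), with three more at 9-week intervals. Section 2.4.2 has the same calendar: "every 6 weeks for the two first boosts (W13 and W19) and every 9 weeks afterward (W28, W37, and W46"). The captions of Figures 1 and 2 repeat it. The entry condition appears only in the Part 2 paragraph.

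That paragraph does not say from when its 4 months run. Elsewhere the article counts from inclusion: section 2.5.7 for the follow-up behind the primary endpoint, and section 2.5.2 for the immunomonitoring samples. Section 2.5.1 allows baseline assessments up to 28 days before first dose.

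**The concern.** An entry condition works only if it is assessed before the treatment it governs. Here the assessment is set at 4 months and the first governed treatment at week 13, roughly 3 months. The week-13 vaccination cannot be counted as induction, because Part 1 lists vaccinations only in weeks 1 to 7 and week 13 is named as a boost under Part 2.

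Following the calendar means boosting patients who have not yet met the entry condition, some of whom may later fail it. Following the condition means the week-13 boost is not given when scheduled. The choice falls before the primary endpoint, so it changes how much vaccine a patient has had when the 4-month response is read. It also changes whether the 4-month immunomonitoring sample is drawn after a boost, which bears on the secondary immune objectives. In a single-arm trial the observed response rate describes the regimen as given, so that regimen should be stated in one way.

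**Working it through.** **Week numbering.** Section 2.4.2 gives the priming phase "at days 1, 8, 15, 29, 36, and 43 (priming phase"), and Part 1 gives the same vaccinations as weeks 1, 2, 3, 5, 6 and 7. The two lists agree if week w starts on day 7(w − 1) + 1: week 2 is day 8, week 5 is day 29, week 7 is day 43.

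**The plan's calendar.** Starting from week 7, steps of 6, 6, 9, 9 and 9 weeks give weeks 13, 19, 28, 37 and 46, exactly as stated. The calendar is consistent in itself. The first boost is due on day 7 × 12 + 1 = 85 and the second on day 7 × 18 + 1 = 127.

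**Date of the 4-month evaluation.** Let D be the length of 4 months: 112 days (two 8-week scan intervals) or 4 × 30.4375 = 121.75 days (calendar months). Let L be the number of days from the time origin to first dose. The evaluation falls on study day 1 − L + D, and the gap after the first boost is (1 − L + D) − 85. L = 0 is counting from first dose. The article does not give the interval from inclusion to first dose, so L = 0 to 28 is an assumption, taken from the 28-day baseline window.

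| L (days) | Evaluation, D = 112 | Gap after day 85 | Evaluation, D = 121.75 | Gap after day 85 |
|---|---|---|---|---|
| 0 | day 113 | 28 | day 122.75 | 37.75 |
| 14 | day 99 | 14 | day 108.75 | 23.75 |
| 28 | day 85 | 0 | day 94.75 | 9.75 |

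The evaluation precedes the second boost in every row, by 127 − 122.75 = 4.25 days at the least. Only the first boost is in conflict.

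**The limit case.** Week 13 runs from day 85 to day 91. With D = 112 the evaluation falls within that week only if 113 − L ≤ 91, that is, L ≥ 22. With calendar months it misses the week even at L = 28, by 94.75 − 91 = 3.75 days.

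**Exposure before the evaluation.** There are six priming vaccinations. Without the week-13 boost the count is 6, with it 7. Each vaccination is two injections, one per peptide.

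**Effect on the sample size.** None. Exact binomial calculation of the two-stage rule (stop at 3 or fewer of 14; negative at 13 or fewer of 42) gives a stage 1 futility probability of 0.063 and power of 0.907 at a 45% response rate, and type I error of 0.0246 at 20%. These match the 6.3%, 90.7% and 2.5% in section 2.5.7.

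**The case against.** The best defence has four parts.

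- *Time origin.* A reader might infer a fixed delay of 4 to 5 weeks for every patient. That holds only when 4 months is counted from first dose, whereas the article counts from inclusion where it names an origin. The delay then shrinks and can reach zero. This stands, and the size has to be given as a range. It does not remove the conflict: the two dates meet only if 4 months means 16 weeks and inclusion precedes first dose by about 3 to 4 weeks, and a schedule cannot rest on that.
- *Is the regimen undefined?* A reader might infer that the regimen under test is not defined. The documents do not support that. The boost calendar is identical in four places and the condition appears once. Both readings share all six priming vaccinations and 3-weekly atezolizumab; they differ by one vaccination before the primary assessment. The count of mentions does not show which rule was intended.
- *Do sites differ in practice?* A reader might infer that they already do. Sites work from the full protocol and its visit schedule, which are not shown, and the drawing in Figure 2 is not available here. The contradiction in the article is established; divergent practice is not.
- *Is this only condensation?* An article may leave detail to the full protocol. This is not missing detail, though: two explicit statements in one paragraph conflict. This part of the defence fails.

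**Conclusion.** The point holds as an internal contradiction. As written, the condition for entering Part 2 is assessed about 28 to 38 days after the first Part 2 boost if 4 months runs from first dose. It is assessed about 0 to 38 days after if 4 months runs from inclusion and inclusion is 0 to 28 days before first dose. Except in the limit case at the bottom of that range, both rules cannot be followed, and the conflict reaches every patient still on treatment at week 13.

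The consequence is 6 or 7 vaccinations before the 4-month response assessment and the 4-month immune sample. Its effect on the response rate cannot be quantified from the documents. The decision rules, error rates and sample size of the two-stage design stand unchanged.

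**What to change.** Reconcile the Part 2 entry condition with the boost calendar in section 2.4.2, the captions of Figures 1 and 2, Figure 2 itself and section 2.5.1, and carry one version through the protocol and the eCRF. State the origin from which the 4 months of the entry condition run. Which rule applies, and whether the condition or the calendar changes, is for the clinical team; the documents do not settle it.

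Record for each patient the number of vaccinations received before the 4-month assessment, and present it as descriptive exposure data only. Response rate should not be reported by that number. It is a post-baseline quantity that depends on staying on treatment to week 13, so patients who progress early have fewer vaccinations by construction and the comparison would mislead.

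The cost is a protocol clarification or amendment and an eCRF check, with no added patients or visits.

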##### - Part 3: Atezolizumab Monotherapy

Atezolizumab in monotherapy will be administrated every 3 weeks until disease progression or unacceptable toxicities for a maximum of 1 year since the last vaccine.

#### 2.5.2 Evaluation, Laboratory Tests and Follow-Up

For the primary end-point analysis, a total body CT scan will be performed at baseline, and every 8 weeks until progression. Additional total body CT scan could be performed if clinically indicated.

For immunological safety assessment, three blood samples will be collected:

Sample N°1: At inclusion visit before the first treatmentSample N°2: At week 5 (before vaccination n°4)Sample N°3: At 2 months from inclusion

In case of immune-related adverse event, these analyses will be performed:

- Immunological blood analysis: IgG, IgE, circulating antibodies (ANA and TPO), CRP, and ferritin. Serum (one dry tube, 6 ml) will be frozen for the measure of anti-telomerase peptide (anti-UCP) antibodies.- Cytokines release measurement (one EDTA tube, 6 ml): Plasma will be frozen for analysis of IL-1b, IL-6, IL-8, IL-2, TNFα, IFN-g, IL-17, and sCD25.

For immunomonitoring analysis, four blood samples will be collected at the following:

Sample N°1: at baselineSample N°2: at 2 months from inclusionSample N°3: at 4 months from inclusionSample N°4: at the end of vaccine visit

Biomonitoring Blood Samples: Six 6-ml EDTA tubes for PBMC collection, one 6-ml EDTA tubes for plasma collection, and one 6-ml EDTA tube for ctDNA collection will be collected for analysis.

#### 2.5.3 Biological Analyses

Specific anti-tumor immune responses and HPV circulating DNA analysis will be performed in collaboration with UMR1098 INSERM/EFS/UFC team and with the Cellular and Molecular Laboratory and the Pathological Laboratory of the University Hospital of Besançon

Immunohistochemistry analysis of anti-tumor responses: Immunohistochemistry analysis will be performed to evaluate p53, p16, and anti-tumor responses to: Class I CMH, Foxp3, pSTAT3, T-bet and immune infiltrates, CD8, and GRZM. This analysis will be performed on tumor samples.Genotyping: Genotyping will be performed on tumor samples obtained by biopsies at diagnosis. This analysis will be performed to characterize the genomic profile of cancers and to determine the influence of the neoantigen charge on the combination therapy. If the tumor sample is sufficient, RNAseq analysis will be performed to determine biomarkers that predict the efficacy of the combination therapy. HPV genotyping will be carried out using the INNO-LiPA technique. In addition, a search for the viral genome integration *via* E6, E7, and E2 proteins will be carried out.Quantification of circulating HPV DNA in plasma by qPCR targeting E6 and E7 will be done before and during treatment.Peripheral blood immune phenotyping and plasma-derived biomarkers- Monocytes and MDSC will be phenotyped by flow cytometry- Regulatory T lymphocytes (CD3/CD4/CD25/Foxp3/CD45RA, CD15s, and CD127)- Immune checkpoint and costimulatory molecules will be analyzed on CD8 and CD4 T-cell lymphocytes (PD-1, TIM3, TIGIT, LAG3, CD226, OX40, 41BB, CTLA4, and CD26)- Angiogenic-related growth factors will be monitored in the plasma of included patients at baseline and 2 months after treatment initiationAssessment of antigen-specific T cells- Peripheral blood mononuclear cells will be exposed to E6, E7, and hTert-derived peptides. CD4- and CD8-specific T-cell IFN-γ production will be monitored by ELISpot IFN-γ. Similar experiments will be performed using TIL.

These experiments will allow us to determine the presence of antigen-specific T cells before and after treatment as well as the ability of combined vaccination and atezolizumab therapy to enhance the diversity of immune responses (epitope spreading).

#### 2.5.4 Tumor Samples Collection

A fresh tumor biopsy for TIL production proof of concept will be performed and centralized at baseline and at 2 months. Collection of tumor biopsies will be guided by ultrasound or CT scan. Methods for TIL culturing were the same as those used by the Rosenberg group (25).Tumor samples obtained by biopsies or surgery at diagnosis will be centralized for the translational research program.

#### 2.5.5 Quality-of-Life Assessment

A health-related QoL EORTC QLQ-C30 questionnaire will be collected:

- at inclusion,- every 8 weeks until the end of treatment visit, and- at the end of vaccine visit.

#### 2.5.6 Data Analysis

For each patient enrolled in VolATIL study, the investigators will document all required data in the corresponding source documents. These data will then be entered in the electronic case report form (eCRF), which will be accessible only to authorized persons **
*via*
** a secured web connection. One eCRF will be created for each patient. The investigator has the responsibility for its completion, proof reading, and its approval after the final verification for the authenticity and accuracy of all entered data. University Hospital of Besançon (Sponsor) will ensure that the study is conducted in accordance with the Good Clinical Practice guidelines and all applicable local laws and that the rights, security, and wellbeing of the patient are respected. The Sponsor will perform source document verification and validation as well as request clarification to ensure the accuracy, completeness, and reliability of data. At the end of the data handling process, a data review meeting will be held to prepare the database lock. After the database lock, data will be transferred into SAS format. Methodology and Quality of Life Unit in Oncology from the University Hospital of Besançon will produce statistical analyses.

#### 2.5.7 Statistical Considerations

VolATIL trial is a one-arm two-stage phase II design. The aim is to demonstrate that the ORR at 4 months according to iRECIST is clearly above a low rate (such as 20%) that would be not satisfactory. The following hypotheses will be considered:

- H0 (null): An ORR rate at 4 months of 20% is uninteresting- H1 (alternative): An ORR rate at 4 months of 45% is expected

According to Simon two-stage design (optimum method) with a one-sided 2.5% type I error and power of 90%, 42 evaluable patients at 4 months will need to be included in order to test the previous hypotheses.

The hypotheses regarding an uninteresting rate of 20% are based on previous studies (17–20, 22–24, 26). An anticipated ORR rate at 4 months of 45% would be considered clinically meaningful.

**Stage 1**: After recruitment of the first 14 evaluable patients with a 4-month follow-up from inclusion,

if three or less than three patients present an objective response at 4 months (21.4%), the treatment could be declared uninteresting. No more additional patients will be included in this armif 4–14 patients present an objective response at 4 months, 28 additional patients will be enrolled in the study.

The probability to conclude for futility at the end of stage 1 whereas p = 45.0% is β1 = 6.3%. This early look interim analysis is planned to look for an early efficacy and safety data.

**Stage 2**: After recruitment of 42 evaluable patients with a follow-up of 4 months from inclusion,

if 13 or less than 13 patients present an objective response at 4 months (≤ 31.0%), the treatment will be declared uninterestingif 14 or more than 14 patients present an objective response at 4 months (≥ 33.0%), the treatment will be regarded as interesting for further evaluation in a phase III trial.

Of note, the rational for H1 hypothesis is sustained by the results of HPV vaccination combined with nivolumab where an ORR of 33% was observed (27).

The probability to conclude for futility at the end of stage 2 whereas p = 45.0% is β2 = 9.3% (i.e. power = 90.7%). The probability to conclude for efficacy at the end of stage 2 whereas p = 20.0% is α2 = 2.5%. With an expected 10% rate of patients not evaluable or lost to follow-up at 4 months, it will be necessary to include (42*100)/90 = 47 patients in the study.

An Independent Data and Safety Monitoring Committee (IDMC) will be constituted and will meet for the validation of the passage from stage 1 to stage 2 for the monitoring of toxicities and also for the reviewing of SAEs every 6 months.

In parallel, given that the safety profile of UCPVax and atezolizumab combination has not been evaluated in patients with HPV-positive cancer so far, a semi-continuous monitoring for toxicity using Pocock-type boundary will be performed [probability of early stopping: 0.05, targeted dose-limiting toxicity (DLT) rate: 0.20]. Patient recruitment will be stopped and discussed with the DSMB (Data Safety Monitoring Board) at the end of stage 1 if 7 or more patients of 14 enrolled patients with a 4-month follow-up experience relevant DLT.

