### 2.8 Monitoring and Safety

An “Independent Data and Safety Monitoring Committee” (IDMC) represented by a multidisciplinary team, including physicians from relevant medical disciplines and biostatistical background, is implemented to the following:

✓ ensure the safety and wellbeing of the patients exposed to study treatment through the ongoing review of safety data✓ assure the highest integrity about operation and performance of the trial✓ evaluate ongoing safety data to detect the possibility of an unfavorable early treatment risk. IDMC will meet for the validation of the passage from stage 1 to stage 2 (see the *Statistical considerations* section) for the monitoring of toxicities and also for the reviewing of SAEs every 6 months. IDMC will meet also in case of unexpected toxicities or as requested.

IDMC’s responsibilities are as follows:

✓ to review safety data on an ongoing basis✓ to recommend that the clinical study be stopped early if there is strong evidence that the investigational medicinal products are harming patients✓ to make recommendations regarding modification of the study if there is strong evidence that such change would substantially contribute to the wellbeing of patients.

Safety results and opinion of the committee will be sent to the ANSM (French Health Products Safety Agency) within 10 days after the analyses of tolerance (additional meetings will be performed in any event of a signal that may affect patients’ safety).

The IDMC will independently make its recommendations for continuation or termination of the trial to the appropriate Sponsor contact. The IDMC will maintain records of all its meetings and activities related to the study.

These records will remain confidential until completion of the final analysis at which time they will be forwarded to the Sponsor for appropriate filing.

Members will be aware of data management and quality control procedures and ensure that the data are timely, accurate, and complete.

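### Section 2.5.7 promises semi-continuous toxicity monitoring with a 0.05 stopping probability, but words the recruitment stop as one look at 7 of 14, which stops with probability 1.2% at the 20% DLT rate

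*Protocol article*

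**What the plan says.** Section 2.5.7 (Statistical Considerations) notes that the safety of this combination has not yet been evaluated in HPV-positive cancer, and for that reason commits to toxicity monitoring: "a semi-continuous monitoring for toxicity using Pocock-type boundary will be performed [probability of early stopping: 0.05, targeted dose-limiting toxicity (DLT) rate: 0.20".

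The next sentence gives the only numerical threshold in the article. Recruitment is to be stopped and discussed with the safety board "at the end of stage 1 if 7 or more patients of 14 enrolled patients with a 4-month follow-up experience relevant DLT".

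Stage 1 of the efficacy design is assessed "After recruitment of the first 14 evaluable patients with a 4-month follow-up from inclusion". The full design needs 42 evaluable patients, and 47 are to be enrolled to allow for 10% not evaluable or lost.

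Section 2.8 adds committee review at the passage from stage 1 to stage 2 "for the monitoring of toxicities and also for the reviewing of SAEs every 6 months", ongoing review of safety data, and extra meetings for unexpected toxicity or on request. None of these carries a numerical boundary. Section 2.6 defines the safety analysis on all patients who received at least one dose.

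**The concern.** A semi-continuous boundary is a series of cut-points checked as patients accrue, and its stopping probability accumulates over all those checks. The sentence that states the action fixes a single time, a single denominator and completed follow-up. A committee that followed it to the letter would not act before 14 patients had reached 4 months and would have no threshold for the 28 evaluable patients of stage 2. The 0.05 would not describe what it was doing.

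The follow-up condition raises a second question. Section 2.7 lists severe adverse event and death among the reasons for ending the study early. If only patients with 4 months of follow-up enter the count, the patients with the worst toxicity may be the ones left out.

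**Working it through.** **Inputs, all from section 2.5.7:** target DLT rate 0.20; early-stopping probability 0.05; threshold 7 of 14; 42 evaluable and 47 enrolled patients. The article does not give the boundary's maximum N or look schedule, so both were varied as assumptions.

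**Step 1. Does 7 of 14 fit the stated parameters?** For a Pocock-type boundary, the cut-point at k patients is the smallest r with P(X ≥ r | k, 0.20) ≤ a. The common level a is the largest for which the exact cumulative stopping probability at 0.20 stays at or below 0.05. With a check after every patient:

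| Assumed maximum N | Cut-point at n=14 | Cumulative stopping probability at 20% |
|---|---|---|
| 14 | 7 | 4.0% |
| 28 | 7 | 4.9% |
| 42 | 7 | 5.0% |
| 47 | 7 | 5.0% |

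Grouped schedules (for example looks at 14 and 42, at 14, 28 and 42, or at 7 and 14) also give 7 at n=14, with totals from 3.7% to 4.7%. The printed threshold is therefore reproduced under every assumption tried.

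**Step 2. What does 7 of 14 do as a single look?** P(X ≥ 7) = Σ C(14,x) p^x (1−p)^(14−x), for x = 7 to 14. At p = 0.20 the leading terms are 0.00921 + 0.00202 + 0.00034 + 0.00004, so the sum is 0.0116, or 1.2%. For comparison, P(X ≥ 6) = 0.0439. A single look calibrated to 0.05 would therefore not have produced 7, so the printed value looks like one point of a longer boundary.

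**Step 3. How far apart are the two readings?** Probability of stopping:

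| True DLT rate | Single look, 7 of 14 | Each patient, to n=14 | Each patient, to n=42 (assumed) |
|---|---|---|---|
| 20% | 1.2% | 4.0% | 5.0% |
| 30% | 9.3% | 17.6% | 37.0% |
| 40% | 30.8% | 42.5% | 82.6% |
| 50% | 60.5% | 70.0% | 98.6% |

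The second and third columns both decide by patient 14, so they compare like with like. The last column also includes monitoring through stage 2. The boundary built for 42 patients has itself stopped with probability 37.3% by patient 14 at a 40% rate.

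**Step 4. The denominator.** Suppose 16 patients are treated. Two have a DLT and leave before month 4, and 6 of the other 14 have a DLT. The literal count is 6 of 14, and recruitment continues. Among treated patients it is 8 of 16, or 50%, the same proportion as 7 of 14.

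**The case against.** The strongest reply is that nothing printed is wrong. The 0.05 is cumulative over a boundary and the 1.2% is the tail at one look, so comparing them does not reveal a miscalculation. Steps 1 and 2 support this: 7 is the n=14 point of such a boundary. A reader might infer that the sponsor chose the wrong threshold or miscomputed its error rate, and the document does not support that.

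A reader might also infer that 7 of 14 is the only rule in force. The article says that the semi-continuous boundary will be used, and a journal article commonly leaves the table, look schedule and maximum N to the full protocol, which is not shown. 7 of 14 is the only rule printed, which is a weaker statement. The missing table is not the point.

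Setting 31% against 83% at a 40% DLT rate as the cost of the wording would also mislead, because it compares a decision by patient 14 with one by patient 42. By patient 14 the contrast is 30.8% against 37.3% to 42.5%.

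Nor does the article say that severe toxicity will go unseen. The committee reviews safety continuously, can meet ad hoc and can recommend stopping. The 4-month phrase may mean only an observation window.

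One thing survives all of this. The action sentence confines the stop to the end of stage 1, and a rule so confined is not semi-continuous. The other reviews carry no numerical limit that would take its place.

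**Conclusion.** The point holds as an internal contradiction between two adjacent sentences of section 2.5.7. It is not an error in any figure. Followed literally, the printed stop has a 1.2% chance of triggering at the target DLT rate, so neither semi-continuous nor 0.05 describes it. Read as one point of a running boundary, it is consistent with both. By patient 14, the readings differ by about 3 percentage points at a 20% DLT rate (1.2% against 4.0%) and about 12 at 40% (30.8% against 42.5%), for a boundary ending at 14. The gap is wider if monitoring continues through stage 2. The single-look figures are exact. The boundary figures rest on an assumed maximum N and, for the tables, a check after every patient.

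The denominator is a secondary ambiguity. The wording allows early toxic dropouts to be left out but does not require it, and it does not match the safety population of section 2.6.

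**What to change.** Reconcile the two sentences in one of two ways:

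- State that 7 of 14 is one point of a running boundary that also applies before and after patient 14. Give its look schedule, maximum N and resulting operating characteristics.
- If one look is intended, remove semi-continuous and 0.05, and report the 1.2% stopping probability at a 20% DLT rate.

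In either case, align the DLT count with the section 2.6 safety population. Say how a patient who dies or leaves before month 4 is counted, and how a treated patient still within the 4 months is counted. The cut-points depend on a maximum N that the article does not give, so the sponsor and the safety committee should set them; none is proposed here.

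The cost is a few lines of text and, under the first option, a running DLT count. At an acceptable DLT rate the chance of a pause rises from 1.2% to at most the 5% that the plan already states.
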